### Acceptability

Acceptability will be determined through exit focus groups with a sample of young people who participated in the programme. Focus groups will be arranged in a safe place in a private classroom or office on the school premises. All participating children will be invited to take part in the exit focus groups. Following parental/caregiver consent as well as assent from children themselves, approximately three children per class will be randomly selected and we will aim to include both male and female participants. The exit focus groups will not be conducted by the programme facilitators, but by independent, trained post-graduate psychology students or members of the research team. We intend to conduct at least 1 focus group in each school with up to 6 children in each focus group. Focus groups will be guided by a script which will assess a range of domains including acceptability, understanding, relevance, and helpfulness. Focus group interviews will be audio-recorded with permission from the children.

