### Formative work that informed the intervention development

The design and adaptation of effective preventive interventions require community ownership, cultural flexibility, and fit with the delivery context to maximise effectiveness, appropriate training, and support to deliver, and relevance and acceptability to stakeholders [1, 29]. The intervention presented in this protocol is based on extensive formative work by the investigators. Firstly, this intervention is based on expertise in the use of CBT, programme development and evaluation, and experience of delivering preventive interventions in South African schools. Indeed, previous research by the investigators has demonstrated that existing evidence-based CBT-based activities and programmes can successfully be adapted to be culturally sensitive and to fit within the South African context [29–34, 38, 39]. Secondly, the intervention is informed by a systematic review by the investigators referred to earlier [36]. The findings of the review demonstrated that universal school-based approaches hold promise for reducing symptoms of anxiety and depression amongst CYP and are better delivered in group format and when based on principles of CBT. Thirdly, the intervention is informed by formative qualitative interviews conducted by the investigators with CYP (grades 5–7), school mental health counsellors, parents/caregivers, and teachers. These interviews elicited participant perspectives on what a universal school-based mental health intervention in this setting should look like and who should be involved [40]. Lastly, to adapt the intervention in the context of COVID-19, the intervention is informed by formative follow-up qualitative interviews with CYP (grades 5–7), school mental health counsellors, parents/caregivers, and teachers. These interviews asked participants about the challenges surrounding COVID-19 and various disease containment measures [41].

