### Ethical review and consent

Ethical approval has been obtained from Stellenbosch University’s Research Ethics Committee: Social Behavioural and Education Research (project number: 9183), and reciprocity has been received from the Psychology Research Ethics Committee (reference number: 19-073) at the University of Bath. The WCED approved of the study being conducted in the two schools (reference: 20200214-4483).

All grade 5 children in both schools will be informed about the intervention and will be given a project information sheet to take home. The information sheet will include an opt-out consent form to be returned if parents/caregivers do not wish their child to be part of the intervention. In addition, children will also be asked to complete assent forms prior to completing baseline assessments. Children whose parents do not agree to participate or who themselves do not provide assent will be supervised in a separate classroom. Children will not be required to provide reasons for not taking part. Once consent and assent have been received, post-graduate psychology students will administer the baseline battery of measures to children one class at a time. The programme facilitators will be on standby should children require individual assistance with the completion of the measures.

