#### Translation of measures

Each of these measures is available freely in the public domain for research purposes. These measures as well as the programme will be available in both English and Afrikaans. All the measures are available in English. Measures not available in Afrikaans were professionally translated into Afrikaans and professionally and independently back translated into English. The translations were checked for accuracy by first language Afrikaans-speaking members of the research team (SH, HG, HL, NM).

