#### Intervention facilitators’ training and supervision

Intervention facilitators will have at least an undergraduate degree in psychology or social sciences and will attend a 2-day training workshop covering the theoretical underpinnings of CBT, specific training on the format, content and delivery of the programme, and procedures for monitoring and evaluation. Both facilitators will be assisted by post-graduate psychology students and/or school mental health counsellors from the NGO, who will act as observers during the facilitation of the lessons. All intervention facilitators will have attended a 2-day training workshop covering the theoretical underpinnings of CBT, specific training on the format, content and delivery of the programme, and procedures for monitoring and evaluation. The training is structured to be a combination of didactic instruction and skills development through role play and reflective discussions. For the purposes of fidelity to the programme and to discuss delivery issues, NM (who has expertise in teaching and in delivering CBT-based mental health interventions to young children in South Africa) and/or HL (who is a counselling psychologist and lecturer with expertise in the development, implementation, and evaluation of CBT-based anxiety interventions for youth in South African) and/or BC (a lecturer and researcher in child mental health and study principal investigator (PI)) and/or ML (who is a clinical psychologist and lecturer with extensive experience of delivering CBT to children and young people) will conduct 1 h of supervision with the lead interventionist and co-facilitator after each step of the programme has been delivered. As such, the programme facilitators will receive 4 h of supervision from an experienced CBT practitioner during the course of the programme.

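### The moderator rule for the exit focus groups bars the facilitators but admits research-team members who developed or supervise the programme, and does not define independence for students

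*Protocol article*

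**What the plan says.** The Acceptability section makes the focus groups the means of judging acceptability: "Acceptability will be determined through exit focus groups with a sample of young people who participated in the programme". It then sets a rule on who may run them. One class of person is excluded: "The exit focus groups will not be conducted by the programme facilitators". Two are allowed, since the sentence goes on "but by independent, trained post-graduate psychology students or members of the research team". A script guides the groups, and they are audio-recorded if the children agree.

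Three other sections describe the people whom these labels cover:

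- Formative work that informed the intervention development: "The intervention presented in this protocol is based on extensive formative work by the investigators".
- Intervention facilitators' training and supervision: four study-team members, the principal investigator among them, are listed with and/or. They "will conduct 1 h of supervision with the lead interventionist and co-facilitator after each step of the programme has been delivered".
- The same section, on lesson staffing: "Both facilitators will be assisted by post-graduate psychology students and/or school mental health counsellors from the NGO, who will act as observers".

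**The concern.** By excluding the facilitators, the authors recognise that someone tied to the programme should not ask children what they thought of it. The second permitted class partly undoes that protection, because it can include people with at least as strong a tie to 4STMF: those who built it and those who supervise its delivery. For the first class, the protection rests on one undefined word.

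Acceptability is half of the primary objective. Children aged about 10 to 13 may hold back criticism in front of an adult whom they connect with the programme. A developer or supervisor may also probe criticism less, without meaning to. Either would tilt the answers towards approval. The Data analysis section also relies on these interviews to explain feasibility shortfalls, such as sessions that were not completed, so the effect could reach beyond the acceptability finding.

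**Working it through.** The document states no figure on this point and gives none from which a bias could be calculated. The check is a comparison of sections.

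**1. Does the research team include people who supervise or developed the programme?** Translation of measures uses the label for a group that checked the Afrikaans versions, "first language Afrikaans-speaking members of the research team". Two of the people identified there are also among the four listed as supervisors in Intervention facilitators' training and supervision. The label therefore covers at least two potential supervisors. Table 1 says that supervision deals with problems of delivery and content, so a supervisor who moderated would already have heard the facilitators' account. On development, the formative-work section refers to the investigators. The supervision section lists the principal investigator among the supervisors, so these circles overlap, although the article never equates them.

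**2. Does the word independent reach the research team?** Two readings are possible.
- If it qualifies only the students, the rule allows a developer or supervisor to moderate.
- If it qualifies both classes, it conflicts with step 1 for those members, and nothing says which members qualify.

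The sentence needs tightening on either reading.

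**3. Who are the post-graduate psychology students?** The description appears in three roles: moderators (Acceptability), assistants and observers in lessons (Intervention facilitators' training and supervision), and administrators of the baseline measures (Ethical review and consent: "post-graduate psychology students will administer the baseline battery of measures to children one class at a time"). Table 1 also draws observers, and some delivery staff, from masters-level psychology students. Only the moderators are called independent. No sentence says that a lesson observer will moderate, and none rules it out.

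**4. What other evidence on acceptability is planned?** Feasibility trial objectives adds consent and assent rates, session and programme completion rates, and a teacher evaluation form. The Feasibility section presents its list as covering both feasibility and acceptability. None of these asks children for their opinion of the programme. Attendance at lessons given in school time says little about liking, and teachers are not the recipients. The focus groups are thus the only planned direct account from children, but not the only evidence.

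**5. How much focus-group data is there?** The stated minimum is one group per school with up to 6 children each, so at most 2 × 6 = 12 children at that minimum. Selecting about three per class from the 6 + 8 = 14 classes given in Characteristics of participants would mean about 3 × 14 = 42. Neither figure gives the size of a moderator effect.

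**The case against.** The strongest reply has four parts.

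- **Students.** The permitted students are expressly called independent. Set against the exclusion of facilitators, the natural meaning is students who did not help in the lessons. A reader might infer from the shared description that lesson assistants will moderate. The document does not support that: it shares a label, not named individuals, and observers may instead be NGO counsellors. This part of the reply stands. What remains is an undefined word, not a stated permission.
- **Research team.** Not every member need be a developer or supervisor, and Table 1 refers separately to a core research team. Supervisors meet the facilitators, in person or remotely, and no section places them in lessons, so children may not know who they are. This weakens the argument that children would hold back. It does not answer the argument about the moderator's own stake, and the rule still admits these people.
- **Safeguards.** The script limits variation in questioning, and the recording allows a later check. Both help, but neither changes who asks the follow-up questions.
- **Level of detail.** Naming each moderator and setting a rota can be left to a fuller protocol. That is fair for the rota. The eligibility rule, however, is stated in the article and is too wide as worded.

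**Conclusion.** The point holds as a limited one. As written, the plan permits a programme developer or supervisor to run the only direct enquiry into children's views, and it leaves student independence undefined. The result is a risk of favourable bias in part of the primary objective.

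Two stronger conclusions are tempting and are not supported. The first is that the children's verdict will be biased upward: the document shows an opening for bias, not its presence or size, and any percentage would rest on invented inputs. The second is that the acceptability conclusion depends on the focus groups alone: rates and the teacher form also contribute.

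The verdict rests on one assumption, that a moderator's link to a programme can affect what children say or how they are probed. This is plausible at this age in a school setting, but the document offers no evidence on it. Nothing in the trial is invalidated. This is an inexpensive improvement, and it has to be made before the interviews take place.

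**What to change.** Amend the moderator sentence in the Acceptability section in two respects:

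1. Limit research-team moderators to members with no role in developing 4STMF or supervising its delivery.
2. State that an independent student is one who did not assist or observe in the lessons of the children in that group. One way to meet this is to cross students over, so that those who observe in one school, or one set of classes, moderate in the other.

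Where staffing or language (English or Afrikaans) prevents this, report each moderator's role alongside the focus-group results as a limitation.

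The cost is a sentence or two of text and less freedom in scheduling. The change draws on students whom the plan already names. The article does not give their number or languages, so whether the crossover can be met in full without extra staff cannot be confirmed; the reporting option covers that case. No additional data collection is needed.

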### Psychological well-being

We will undertake an exploratory analysis of our psychological measures. The purpose will be to (i) inform decision-making about which will be our primary outcome in a subsequent trial and (ii) to inform the power calculation for a subsequent RCT. The following standardised psychological measures will be completed at each assessment.

#### Symptoms of depression and anxiety

We will use the Revised Child Anxiety and Depression Scale-30 (RCADS-30) [43] to measure symptoms of depression and anxiety. The 30-item measure asks participants to rate their responses on a 4-point Likert scale from ‘never’ to ‘often’. The measure has good psychometric properties, and amongst a South African sample of adolescents, the 10-item depression subscale showed good internal consistency (alpha coefficient = 0.86) [44].

#### Happiness and well-being

We will use the happiness and well-being measure developed as part of the PACES trial [45]. The 7-item, visual analogue scale measures happiness about the school, appearance, family, friends, home, health, and life in general.

#### Emotion regulation

We will use the 10-item Emotion Regulation Questionnaire for Children and Adolescents (ERQ-CA [46];) to measure emotion regulation strategies of cognitive reappraisal (6 items) and expressive suppression (4 items). The measure has sound internal consistency and shows stability over 12 months.

#### Bullying

We will use the 2-item Olweus Bully/Victim Questionnaire-Modified [47]. Response options are given on a 5-point rating scale (0 not at all, 1 = once or twice, 2 = two or three times a month, 3 = about once a week, 4 = several times a week). The measure has 9 items; however, we will only use two. We use the two items used as part of the PACES trial [45] in which children are asked about how often they have been bullied, and how often they have taken part in bullying other children.

#### Self-esteem

We will use the 10-item Rosenberg self-esteem scale [48]. Rosenberg’s Self-Esteem Scale is the standard measure of self-esteem in psychological research. The scale provides a short, straightforward, and convenient method for measuring global self-esteem. Items are measured on a 4-point rating scale from 1 (strongly agree) to 4 (strongly disagree).

#### Goal setting

We will use the 5-item goal setting scale [49]. Reliability analyses yielded an alpha of 0.68 for this scale.

#### Stressful life events in the past 7 days

The revised child impact of events scale (CRIES) (at post-intervention only) [50]. This measure contains a screening question at the beginning to assess for eligibility for completing this measure. As such, not all children will necessarily be eligible to complete this measure in full.

#### Translation of measures

Each of these measures is available freely in the public domain for research purposes. These measures as well as the programme will be available in both English and Afrikaans. All the measures are available in English. Measures not available in Afrikaans were professionally translated into Afrikaans and professionally and independently back translated into English. The translations were checked for accuracy by first language Afrikaans-speaking members of the research team (SH, HG, HL, NM).

### Randomisation and blinding

Two schools were randomly selected from a list of 21 schools within which the NGO operates. These two schools were then randomised to either immediate or delayed delivery of 4STMF. By the nature of the intervention, neither the participants nor the interventionists were blind to arm.

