**Methods:**

This is a feasibility pilot study of 4 Steps To My Future (4STMF), a Cognitive Behaviour Therapy (CBT) school-based programme for young adolescents in the Western Cape, South Africa. This eight-session intervention will be delivered to children in grade 5 (aged 10–13 years approximately) attending two public government-run schools in the Western Cape, South Africa. We aim to enrol approximately 224 children in grade 5. We will randomise which school receives the intervention first and the other will be a delayed intervention group. We will train individuals with a post-graduate degree in psychology to facilitate the programme. We will collect demographic data on participants as well as data on primary (feasibility measures) and secondary outcomes (mental health and well-being measures). We will collect data at baseline, post-intervention, and at 1-month follow-up.

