### Trial design

We will conduct a two-arm, randomised, feasibility pilot trial comparing immediate intervention group (IIG) delivery of 4STMF to a delayed intervention group (DIG). The consort diagram of the study design is shown in Fig. 2.

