### Characteristics of participants

Participants will be in grade 5 at participating schools (aged ~ 10–13 years). The intervention will be universally delivered, i.e. delivered to all participating children regardless of symptomatology or risk. Given the restrictions posed on this research by COVID-19 and given changes to school scheduling, we pragmatically decided to target the intervention at one grade, grade 5, only. There are approximately 20 eligible children per class with 6 and 8 classes at our target schools respectively. As such, whilst there are approximately 280 children eligible to take part in grade 5 across these 2 schools, we expect a sample of approximately 224 children to take part in this study which accounts for a 20% non-participation rate. We will calculate consent and retention rates at immediate post-intervention as well as 1-month follow-up. As per communication received from the Western Cape Education Department (WCED), no research may be conducted during the fourth term (October–December 2021) as schools are preparing and finalising syllabi for examinations. This could then mean that a 1-month follow-up assessment might not be possible with the children in the DIG.

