#### Data analysis

Descriptive statistics will summarise our feasibility outcomes and demographic data. Quantitative data will be analysed using SPSS and other statistical software, as appropriate. Participant characteristics will contain both continuous and categorical variables. We will use means and standard deviations to summarise data collected on the continuous variables and frequencies and percentages to summarise data collected on the categorical variables. An exploratory analysis of the psychological outcomes will be undertaken. Analysis will involve pre- and post-comparisons within and between groups exploring baseline, post-intervention, and 1-month follow-up data.

Qualitative data will be transcribed verbatim and will be uploaded into ATLAS.ti 9 to be analysed deductively and/or inductively using both content analysis and thematic analysis [51]. Qualitative data will be focus group data collected from learners on completion of intervention delivery at both schools.

The findings obtained from our qualitative formative work were used to inform the development of the intervention material. Similarly, we will integrate both quantitative and qualitative data obtained from this feasibility and acceptability pilot study in our reporting of the main study outcomes. We will do so by providing descriptive data on our feasibility outcomes and complementing these numerical data with qualitative data obtained from our exit interviews. These exit interviews may then help us to understand qualitatively, for example, why the intended number of sessions was not completed.

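### With one school per arm, the exploratory between-group comparison cannot be separated from school and should be descriptive only

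*Protocol article*

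**What the plan says.** The Abstract states the allocation plainly: "We will randomise which school receives the intervention first and the other will be a delayed intervention group". The Randomisation and blinding section agrees: after two schools were drawn from a list of 21, "These two schools were then randomised to either immediate or delayed delivery of 4STMF". The Trial design section labels the result a randomised comparison of two arms, immediate (IIG) against delayed (DIG).

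For the psychological outcomes, the Data analysis section commits to a between-group element: "Analysis will involve pre- and post-comparisons within and between groups exploring baseline, post-intervention, and 1-month follow-up data". The Psychological well-being section gives the status of this work, "We will undertake an exploratory analysis of our psychological measures", and two purposes: to help choose the primary outcome of a later trial and "to inform the power calculation for a subsequent RCT". The Feasibility trial objectives section also ties changes from before to after the programme to the future sample size. The same section makes acceptability and feasibility the primary objective.

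The article does not mention clustering by school or the overlap of school with arm, and sets no limit on how the IIG–DIG contrast may be read.

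**The concern.** When a single school forms each arm, any difference between arms is also a difference between two schools. The data cannot show how much of it comes from the programme. Because the study is called randomised, a reader could take an IIG–DIG difference as randomised evidence, although the randomisation decided only which school went first.

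What is at stake is the next trial. A psychological measure could look responsive, and be favoured as primary outcome, because two schools happened to drift apart. A difference taken from the contrast could also mis-size the full RCT.

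This is not a detail that a statistical analysis plan could supply. The number of schools per arm is fixed by the design, and no model chosen later can change it.

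**Working it through.** **The plan's own figure.** From Characteristics of participants: "There are approximately 20 eligible children per class with 6 and 8 classes at our target schools respectively", and "we expect a sample of approximately 224 children to take part in this study which accounts for a 20% non-participation rate". So 20 × (6 + 8) = 280 eligible, and 280 × 0.80 = 224, which reproduces. This is a recruitment projection. The article states no alpha, power, effect size, SD or ICC, so there is no power calculation to check.

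**Identifiability.** Between-school degrees of freedom = schools − arms = 2 − 2 = 0. Only two allocations were possible, so the smallest two-sided randomisation p-value is 2/2 = 1.0. No between-school variance can be estimated apart from the arm effect.

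**Illustration 1: one time point, children treated as independent.** Expected arm sizes are 120 × 0.8 = 96 and 160 × 0.8 = 128. The article does not say which school is in which arm, and the results do not depend on it. With the outcome SD set to 1 and the school ICC assumed:

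- Naive SE = √(1/96 + 1/128) = 0.135
- True SE = √[2·ICC + (1 − ICC)(1/96 + 1/128)]
- Type I error at nominal 5% = 2[1 − Φ(1.96 × 0.135 / true SE)]
- Floor on the SE with unlimited children = √(2·ICC)

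| Assumed school ICC | True SE | SE floor | Type I error |
|---|---|---|---|
| 0.01 | 0.195 | 0.14 | 17.5% |
| 0.02 | 0.241 | 0.20 | 27.1% |
| 0.05 | 0.343 | 0.32 | 44.0% |

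The floor column shows why more children in the same two schools do not solve the problem.

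**Illustration 2: change from baseline.** This is closer to the planned analysis. Further assumptions are a within-child correlation of 0.6 and a correlation c of 0.5 to 0.9 between a school's effects at the two time points.

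- Naive variance = 2(1 − ICC)(1 − 0.6)(1/96 + 1/128)
- True variance = 4·ICC·(1 − c) + naive variance

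Lowest case (ICC 0.01, c = 0.9): naive SE 0.120, true SE 0.136, type I error 8.3%. Highest case (ICC 0.05, c = 0.5): naive SE 0.118, true SE 0.337, type I error 49.4%.

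Taking change removes stable school differences. What remains is a school's own movement over time, which is still aliased with arm. The article gives reasons to expect some: the Intervention section lets each school settle the timing of lessons, Table 1 allows weekly or twice-weekly delivery according to the school, and the Discussion foresees COVID-19 disruption.

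**The case against.** The strongest reply is that this is a feasibility pilot. Its primary outcomes (opt-out, assent, completion, attendance and fidelity) are summarised descriptively, and one school per arm does them no harm. The psychological analysis is labelled exploratory and no effectiveness conclusion is promised. This stands. A reader might infer that the pilot as a whole is invalid; the documents do not support that.

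Second, the article names no hypothesis test, alpha or model. A reader might infer that a child-level test with an 18% to 44% error rate is planned. It is not stated. Those figures describe a hypothetical analysis of raw scores, whereas the article plans comparisons involving baseline. They are kept only to show scale, alongside the change-score range.

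Third, the article never says that the IIG–DIG difference will supply the future effect size. SDs and completion rates are ordinary inputs to a power calculation and do not depend on that contrast. This also stands: the stated purposes leave such use open but do not announce it.

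Fourth, the Study setting section describes similar schools in staffing ratio, size and nutrition-programme status. This may reduce imbalance and bears on how large an ICC is plausible, but it does not separate school from arm.

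Finally, one might hope to recover an estimate from the delayed school's later period, or by modelling class. The first works only by assuming no school-by-time difference, which two schools cannot test. The second does not absorb variation between schools, so its intervals would still be too narrow.

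**Conclusion.** The point holds as a limit on one secondary, exploratory comparison. Arm and school are completely aliased, and this rests on the stated design alone, without any assumed figure. The IIG–DIG contrast can be described, but it gives neither an unconfounded programme effect nor a valid standard error.

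The size of the possible error does depend on assumptions, because no ICC or correlation is given: about 18%, 27% and 44% at one time point for ICC 0.01, 0.02 and 0.05, and about 8% to 49% for change scores. All of these apply only if children were analysed as independent.

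The point is worth correcting because the psychological results are meant to shape the later RCT. It does not undermine the primary objective and is not a reason to hold up the study.

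**What to change.** In Trial design and Data analysis:

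- Describe a two-school feasibility pilot in which only the order of delivery was randomised, and state that school and arm cannot be separated. The Abstract wording is already close to this.
- Report the psychological outcomes by school. Show any IIG–DIG difference descriptively, without hypothesis tests or efficacy claims.
- State that this contrast will not be used to choose the primary outcome or set the effect size of the future RCT.
- Use the pilot for SDs, completion rates and class-level clustering within schools, and take the school ICC from outside sources.

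The cost is a few sentences; no further schools or data are needed. The study gives up a comparative claim that its design cannot support.
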